### 4.3 Exclusion criteria

A potential subject who meets any of the following criteria will be excluded from participation in this study:

- An indication for intravenous medication
- Blood pressure >160/110mmHg
- Absent-/or reversed flow umbilical artery Doppler
- HELLP (Table 1)
- Obstetric intervention expected <48 hours, e.g. due to:
  - Non reassuring CTG
  - Active vaginal blood loss
  - Signs of abruption placentae
  - Meconium stained amniotic fluid
  - Signs of chorioamnionitis
- Patients admitted with a clinical diagnosis of sepsis with hypotension (i.e. septic shock).
- Insufficient knowledge of Dutch or English language
- Insufficient comprehension of instruction Nemo Remote® or patient information
- Fetal and/or maternal cardiac arrhythmias
- Contraindications to abdominal patch placement (dermatologic diseases of the abdomen precluding preparation of the abdomen with abrasive paper)
- Patients connected to an external or implanted electrical stimulator, such as Transcutaneous Electro Neuro Stimulation (TENS) and pacemaker (because of disturbance of the electrophysiological signal).

*Table 1. Definitions of pregnancy related diagnosis*

|                                                                                                                                                                                                                                                                                                                                                                                                                                                                                                                                                                                                                                                                                                                                                                                                                                                                                                                                                                                                                                                                           |

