### 5.1 Investigational treatment

All patients will receive routine care following national guidelines and/or local protocols. Participants at the clinic will receive self-administered remote eCTG monitoring by NRM once a day (*Figure 1*). In case of follow-up at the outpatient clinic, participants will receive self-administered remote eCTG monitoring by NRM once per day or at least twice a week, depending on their care path. The realtime eCTG measurement will be instantly transferred digitally to the hospital electronic patient file (Chipsoft HiX) and assessed real-time on interpretability by the HCP. Monitoring will last between 30-90 minutes depending on the interpretability and reassurance of the remote eCTG measurement. Criteria defining a successful measurement are described in a standard operating procedure (SOP) and will be available for HCPs at the hospital to avoid prematurely closing of the eCTG measurement (see section 7.1.1). All HCPs involved in this study will receive training on the study protocol. The study procedure and statistical analysis are described in section 7.3.2, chapter 9 and in *Figure 12*.

Monitoring will be repeated the same day when reassuring but insufficiently interpretable, or upon request of the HCP in case of concerns about maternal and/or fetal condition. Additional detailed information of the NRM is described under investigational product (chapter 6). When remote eCTG interpretability is insufficient – based on clinical assessment of HCPs – a switch to conventional CTG monitoring will take place. In this study, HCPs will be asked to define clearly if a switch to conventional CTG was made based on insufficient interpretability or because of concerns about fetal and/or maternal condition (section 7.1.2).

From the second day onward, synchronized US Doppler measurements (clips of 2 x 5 minutes) of the umbilical and uterine arteries will be performed simultaneously with the remote eCTG for 24 patients ([images removed]

*Figure 3*). Measurements of two groups - cardiovascular low (PPROM; N=12) versus cardiovascular high-risk (PE/FGR; N=12) - will be collected and analyzed to evaluate the feasibility of synchronized multimodal acquisitions of maternal and fetal measurements.

[images removed]

*Figure 3. Measurement fetal and maternal heartrate, Doppler arteria umbilicalis, Doppler uterine artery and uterine activity.*

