#### **6.4.2 Contraindications**

The system is not intended for:

- Use in gestation period < 21 completed weeks
- Use in multiple pregnancies
- Use on patients with dermatologic diseases in which abdominal skin is involved
- Use on patients connected to external or implanted stimulators
- Use during defibrillation, electrosurgery or magnetic resonance imaging (MRI)
- Use in x-ray departments

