#### 6.4.4 Clinical warnings and potential risks

- The system is not a replacement for observation and evaluation of the patient and fetus at set times by a qualified healthcare provider, who makes diagnoses and takes decisions regarding treatment and interventions. For accurate care of the patient and fetus, clinical assessment of the CTG should be combined with knowledge of patient anamnesis and risk factors.

- The system is not designed for:
  - Use during defibrillation, electrosurgery or magnetic resonance imaging (MRI)
  - Use in x-ray departments.

Remove the Patch prior to performing any of the above scenarios, otherwise harm to the patient or damage to equipment may occur.

- From 27 to 36 weeks gestational age, the chance of FHR signal loss is higher due to the presence of vernix caseosa, which can reduce transmission of electrical signals.
- In case clinical decision-making cannot be properly substantiated based on the CTG registration, other observation and monitoring methods must be used.
- In some cases, the use of the Patch, in combination with skin prep, may result in skin irritation. Try to reduce the duration of use and the skin prep as far as possible if the skin is irritated.
- To prevent reduced performance, replace a Patch when its adhesive properties have reduced or the electrode gel has come partially loose.
- To prevent cross-contamination, never reuse a Patch on another patient.
- To prevent the risk of skin irritation, ensure that no cleaning or disinfection agent residues remain on the system.
- The system detects repeating characteristics of the fetal and maternal ECG signal to calculate the fetal and maternal heart rate. If either the pregnant woman or her fetus has a highly irregular ECG, the heart rate may not be calculated correctly and the system may temporarily provide incorrect output. In case clinical decision-making cannot be sufficiently substantiated, other observation and monitoring methods must be used.
- In rare cases, the amplitude of the fetal ECG signal that is measured on the maternal abdomen is in the same order of magnitude as the amplitude of the maternal ECG that is being measured. In these circumstances, interchange of fetal and maternal heart rate may occur. The system will then temporarily display FHR values as maternal heart rate and maternal heart rate values as FHR. In case clinical decision-making cannot be sufficiently substantiated, other observation and monitoring methods must be used.

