- Once the eCTG measurement is considered successful – or when the maximum of 90 minutes has exceeded – the HCP will send a message in the Luscii app® and will contact the participant by telephone a few minutes later, the time they have stopped the remote eCTG measurement. All findings will be discussed with the participant and completed in the patients' file in HiX. In addition, the HCP will visit the participant in the hospital room.
- When eCTG measurement is not successful but reassuring, the measurement will be repeated the same day on a moment agreed between participant and HCP (PA).
- When eCTG measurement is not interpretable after repetition on the first day of inclusion, eCTG will be defined not successful – primary outcome – and a switch to conventional CTG will take place. Equally to routine care, in- hospital care is needed and home- monitoring will not be possible.
- When after an additional clinical visit by the HCP (PA) “unscheduled consult” at participants room for other reasons than signal quality concerns (e.g. contractions, reduced fetal movements, patients concerns), without indication for hospitalization – eCTG adequate and reassuring – participants can continue “home monitoring” through eCTG like it will be once home monitoring is implemented in the future. No switch to conventional CTG will be needed. This additional visit will be recorded as part of the patient journey for later cost analysis purposes (*Figure 11, Table 2*).
- As long as remote eCTG measurements are successful, participants will continue the study interventions until discharge, delivery or when 37 weeks is reached. At any moment – when demanded by the participants or by the HCP – a switch to conventional CTG will be made.
- When reached a GA of 37 weeks, after delivery or at discharge, participants will be asked to fill in a second digital questionnaire (5.1, 7.3.3), and at 4 weeks after delivery a third questionnaire.

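### The skin-disease exclusion in section 4.3 is narrower than the device contraindication in section 6.4.2, so a contraindicated woman could be enrolled

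*Protocol*

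**What the plan says.** Section 4.3 lists as an exclusion: "Contraindications to abdominal patch placement (dermatologic diseases of the abdomen precluding preparation of the abdomen with abrasive paper". The bracket ends with those words.

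Section 6.4.2 lists the uses for which the system is not intended. Two of its entries concern patient characteristics that 4.3 also addresses: "Use on patients with dermatologic diseases in which abdominal skin is involved" and "Use on patients connected to external or implanted stimulators". The 4.3 counterpart of the second begins "Patients connected to an external or implanted electrical stimulator" and then gives examples and a reason.

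Section 6.4.4 adds a warning, "In some cases, the use of the Patch, in combination with skin prep, may result in skin irritation", and advice, "Try to reduce the duration of use and the skin prep as far as possible if the skin is irritated".

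On exposure, section 5.1 states: "Participants at the clinic will receive self-administered remote eCTG monitoring by NRM once a day". Outpatients are monitored once per day or at least twice a week, and a session lasts 30 to 90 minutes. Section 7.3.2 says that, while measurements succeed, "participants will continue the study interventions until discharge, delivery or when 37 weeks is reached". Section 12.1 b gives a general assurance that the device is used only within its intended use.

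**The concern.** The two skin criteria apply different tests. Section 6.4.2 asks whether abdominal skin is diseased. Section 4.3 asks whether the disease rules out abrading the skin. The second group lies inside the first, so some women for whom the device is not intended remain eligible.

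What is at stake is participant safety in a small group, and consistency between the eligibility rules and the device labelling on which the protocol relies. Staff screen against 4.2 and 4.3, and withdrawal for ineligibility under 7.4 is also tied to the inclusion and exclusion criteria. A device contraindication that is weakened in those lists can therefore be missed at screening.

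Being able to tolerate preparation also does not settle whether the patch should be worn. The advice in 6.4.4 for irritated skin is to cut back wearing time as well as preparation, so contact with the patch matters separately from abrasion.

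**Working it through.** The core of the check is a comparison of texts. The only arithmetic concerns exposure.

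**Step 1: compare each patient-level contraindication in 6.4.2 with eligibility.**

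| 6.4.2 contraindication | Eligibility counterpart | Result |
|---|---|---|
| Gestation below 21 completed weeks | 4.2: 32+0 to 36+6 | Tighter |
| Multiple pregnancy | 4.2: singleton required | Matched |
| External or implanted stimulators | 4.3: external or implanted electrical stimulators, with examples and a reason | Carried over without narrowing |
| Any skin disease involving the abdomen | 4.3: abdominal skin disease that rules out abrasive preparation | Narrower |

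The remaining 6.4.2 entries (defibrillation, electrosurgery, MRI, X-ray departments) concern circumstances of use, not patient eligibility. Among the patient-level items, only the skin criterion is looser than the device text.

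**Step 2: is the 4.3 bracket a limit or an illustration?** It carries no *e.g.* or *such as*, although the same list uses both where it means examples. The participle in the bracket qualifies which diseases count. The natural reading is a limit.

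**Step 3: does anything else close the gap?** No criterion in 4.2 or 4.3 excludes abdominal skin disease in general, and none refers to 6.4.2. Section 12.1 b states a principle about device use but gives staff nothing to screen against.

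**Step 4: place a patient.** Take a woman with abdominal skin disease whose clinician judges that the skin can be abraded.
- Under 6.4.2 she is contraindicated.
- Under 4.3 as naturally read she is not excluded.
- If she meets the other criteria she can be enrolled.

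**Step 5: exposure of one such woman, from the protocol's own schedule.**
- Window: 32+0 to 36+6 inclusive = 5 weeks × 7 = 35 days.
- Inpatient ceiling, one session a day: 35 sessions, not counting same-day repeats.
- Outpatient minimum frequency over the same window: 5 weeks × 2 = 10 sessions.
- Session length: 30 to 90 minutes.

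The 35 is an upper bound, reached only with inclusion at 32+0 and no delivery, discharge or switch to conventional CTG before 37 weeks.

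**The case against.** The strongest defence is that the operative words of the 4.3 criterion are its opening ones, which exclude contraindications to placing the patch. Section 6.4.2 is the protocol's own list of contraindications and includes abdominal skin disease, so a woman on that list would already be excluded and the bracket would merely explain why. The next bullet in 4.3 supports this by example, since it ends with a bracket that gives a reason and not a limit.

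This reading is possible but not the natural one. The neighbouring bracket announces itself as a reason by opening with *because*; the skin bracket does not, and its wording selects which diseases qualify. An eligibility rule should not depend on the reader choosing the wider interpretation.

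A second defence is that other safeguards would catch the patient: staff are trained on the protocol, a user manual is available, the investigator or a healthcare professional goes through the procedure with each participant before the first measurement, and 12.1 b commits to intended use. These lower the chance of an error. None is a screening criterion, and 12.1 b is contradicted by the narrower exclusion rather than curing it.

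A third is that 6.4.4 addresses irritation and not pre-existing disease, and advises reducing use rather than stopping it. That is fair. The warning shows only that wearing the patch and abrading the skin are separate concerns; it does not show a serious hazard for mildly affected skin.

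Finally, the consequences are small. This stands. The protocol describes irritation as having a very small probability and needing no treatment, and a switch to conventional CTG is possible at any time. The exposure ceiling is also the same for any participant, so it bounds the consequence and does not measure how often the gap would matter. It remains that the protocol does not show those reassurances to hold for women with abdominal skin disease, whom its device text places outside intended use.

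**Conclusion.** The point holds. As naturally read, 4.3 leaves eligible a group that 6.4.2 rules out, and no other criterion closes the gap. The conclusion rests on reading the bracket as restrictive. A wider reading exists, but the wording does not secure it.

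The point is minor in frequency and expected harm. How many women are affected cannot be stated, because the documents give no prevalence of abdominal skin disease. For one affected woman the exposure would be at most 35 daily inpatient sessions, or 10 sessions over the full five weeks at the minimum outpatient frequency. No effect is claimed on the sample size, the primary success rate or the incidence of skin irritation. The correction should still be made, because it changes who may be enrolled and brings eligibility into line with the device contraindication.

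**What to change.** Reword the 4.3 criterion to exclude any patient with a dermatologic disease that involves the abdominal skin, and drop the condition about tolerating abrasive preparation. This matches 6.4.2 and makes 4.3 consistent with 12.1 b.

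The cost is a one-line amendment and possibly the loss of a very small number of otherwise eligible women. Nothing in the sample size calculation or the analysis needs to change.

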#### **4.4 Sample size calculation**

In a previous cohort study for conventional remote CTG monitoring, 4% of all tracings needed repetition (562 out of 12,649) and 0.9% (N=111) of the CTGs had to be repeated in the hospital. The success rate at first trace was 95.5% and after repetition 99% (28) .

A success rate of 90% is considered clinically sufficient based on previous studies (28-30) and HCPs' opinion. Only the first day of remote eCTG measurements will be used for determination of the feasibility by assessing the signal quality and success. If the remote eCTG measurement is technically insufficient but reassuring – according to current clinical policy – it can be repeated once at the same day and still be considered successful. Calculated on 90% chance of success according Wilson standard error of proportions (CI95% > lower limit of 82.5%), 60 subjects are needed for inclusion in this cohort study.

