### 3. STUDY DESIGN

The study will be conducted as a single center prospective cohort study between November 2024 and April 2026, aiming to include 60 eligible patients between 32 and 37 weeks of gestational age. The study is situated at the obstetric department of the Máxima Medical Center (MMC), a secondary and tertiary maternity care unit. However the aim of this study is to evaluate home monitoring in a hospital setting (Home@Hospital), only the use of remote eCTG through a NRM connection will differ from the standard care. A detailed description of the study population including sample size calculation, treatment of subjects, methods and statistical analysis, is provided in chapters 4,5,7 and 9. For study design and study procedures see Figure 2. The study will be registered on 'ToestingOnline' and 'www.clinicaltrials.gov'.

[figure not shown]

Figure 2. Flowchart of the HASTA prospective cohort design and study procedures.

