## 9. STATISTICAL ANALYSIS

### 9.1 Primary study parameter(s)

Primary data statistical analyses will be performed using SPSS version 29 (IBM Corp., Armonk, NY, USA) and SAS software version 9.4 (SAS Institute Inc., Cary, NC, USA). Signal quality will be defined as the percentage of time (minutes) in which the remote eCTG device delivers an FHR value. Signal quality will be determined for each patient. Mean, SD, and 95% confidence interval (CI) of the mean success rate will be calculated using a one-sample t-test. The one-way ANOVA analog, Kruskal-Wallis test will be used in when no normal division of outcomes is found. Success rate will be defined as the number and percentage (N/%) of remote eCTG registration the first day of inclusion with at least 30 minutes interpretable signal quality and/or less than 20% signal loss during 30 to 90 minutes measurement (see section 7.1.1).

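### N=60 does not give the Wilson 95% lower limit above 82.5% that section 4.4 states for a 90% success rate, and section 9.1 uses a different interval and carries over neither figure

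*Protocol*

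**What the plan says.** Section 4.4 gives a benchmark for the primary outcome: "A success rate of 90% is considered clinically sufficient based on previous studies (28-30) and HCPs' opinion". It says which data answer the question: "Only the first day of remote eCTG measurements will be used for determination of the feasibility by assessing the signal quality and success". It then derives the sample size: "Calculated on 90% chance of success according Wilson standard error of proportions (CI95% > lower limit of 82.5%), 60 subjects are needed". The 82.5% figure appears only in that last sentence.

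Section 9.1 defines the measure: "Success rate will be defined as the number and percentage (N/%) of remote eCTG registration the first day of inclusion". For the analysis it states: "Mean, SD, and 95% confidence interval (CI) of the mean success rate will be calculated using a one-sample t-test". It gives no reference value for the t-test, mentions neither 90% nor 82.5%, and does not use the Wilson interval on which section 4.4 relies.

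**The concern.** Section 4.4 puts two figures side by side for the same day-1 proportion: an adequate rate of 90%, and a lower confidence limit above 82.5%. A reader would expect a study that observes exactly the planned 90% to satisfy both. With 60 patients it satisfies the first and misses the second. Section 9.1 then analyses the proportion with another interval and refers to neither figure.

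Two things are at stake. The precision claimed for the design is not delivered at N=60. And because planning and analysis use different intervals, whether a result near 90% clears 82.5% depends on the interval chosen. That choice, and the choice of which figure counts, could be made after the data are seen.

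**Working it through.** **Inputs.** Expected rate 0.90, lower limit 0.825, Wilson method and n = 60 are from section 4.4; the t-based interval is from section 9.1. Sidedness is not stated. I take the 95% interval as two-sided (z = 1.96) and also show the one-sided result. I apply the section 9.1 t-interval to the 0/1 success indicator, one result per patient.

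**1. Can N = 60 be reproduced?** The smallest n whose lower limit at p = 0.90 reaches 0.825 is:
- two-sided Wilson, the named method: 99
- one-sided Wilson: 70
- two-sided Wald: 1.96² × 0.90 × 0.10 / 0.075² = 61.5, so 62

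Only the two-sided Wald interval comes close to 60, and it is not the named method. Even so, at n = 60 it gives 82.4%, just short of 82.5%.

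**2. Wilson lower limit at n = 60.** The formula is [p + z²/(2n) − z√(p(1−p)/n + z²/(4n²))] / (1 + z²/n), with z²/(2n) = 0.0320 and 1 + z²/n = 1.0640.
- 54/60 (90.0%): (0.9320 − 0.0824) / 1.0640 = 0.799
- 55/60 (91.7%): (0.9487 − 0.0769) / 1.0640 = 0.819
- 56/60 (93.3%): (0.9653 − 0.0708) / 1.0640 = 0.841

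An observed 90% needs 54 successes. A two-sided Wilson lower limit above 82.5% needs 56.

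**3. The interval planned in section 9.1.** Lower limit = p − t(0.975; 59) × s/√60, with t = 2.001.
- 54/60: s = 0.3025, s/√60 = 0.0391, so 0.9000 − 0.0782 = 0.822
- 55/60: s = 0.2787, s/√60 = 0.0360, so 0.9167 − 0.0720 = 0.845

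**4. Lower limits side by side at n = 60**

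| Successes | Two-sided Wilson | One-sided Wilson | Two-sided Wald | t (section 9.1) |
|---|---|---|---|---|
| 54 | 79.9% | 81.8% | 82.4% | 82.2% |
| 55 | 81.9% | 83.9% | 84.7% | 84.5% |
| 56 | 84.1% | 86.0% | 87.0% | 86.8% |

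At 54/60 all four fall short of 82.5%. At 55/60 only two-sided Wilson does.

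**5. How likely each outcome is**, from Binomial(60, p)

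| True rate | At least 54 | At least 56 | 54 or 55 |
|---|---|---|---|
| 82.5% | 8.1% | 1.4% | 6.7% |
| 85% | 18.5% | 4.2% | 14.3% |
| 90% | 61% | 27% | 34% |
| 95% | 97% | 82% | 15% |

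At a true 90%, exactly 54 has probability 0.169 and exactly 55 has 0.166. The two figures disagree with a chance of about 34% under two-sided Wilson and about 17% under the t-interval, where only 54 conflicts.

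**6. Does the disagreement survive a corrected N?** No. At n = 99, 89 successes is 89.9% with a Wilson lower limit of 82.4%, which misses both figures; 90 successes is 90.9% with 83.6%, which meets both. At n = 100, 89 successes gives 81.4% and 90 gives 82.56%, so both figures again need 90.

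**The case against.** The strongest reply is that 82.5% is a precision target used to choose N, not a criterion. It stands only in the sample-size sentence, the primary objective in section 2.1 is to estimate a percentage, and nowhere does the protocol say that feasibility fails if the lower limit is 82.5% or less. This stands. A reader might infer that 54 or 55 successes would be declared both feasible and not feasible. The protocol does not support that, because it states one clinical benchmark and no pass/fail rule on the limit.

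A reader might also infer that the two figures conflict in principle, whatever the sample size. Step 6 shows otherwise: the gap comes from N = 60 being too small for two-sided Wilson. The 55/60 case, moreover, disappears under the interval that section 9.1 plans.

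Finally, a formal decision rule may properly sit in a statistical analysis plan, which is not at hand, so its absence alone is no fault. What remains is in the protocol's own text. Read purely as a precision target, 82.5% is still not reached at 54/60 under the named method or under the interval planned for the analysis, and sections 4.4 and 9.1 use different intervals for the same proportion.

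**Conclusion.** The point holds in this form. At the planned 54/60, the two-sided Wilson lower limit is 79.9% rather than above 82.5%, a shortfall of 2.6 percentage points. At N = 60 the stated limit is met only from 56/60, with a chance of 27% at a true 90% and 82% at a true 95%. The two figures in section 4.4 disagree at 54/60 under either interval, and also at 55/60 under two-sided Wilson. The cause is a sample size that does not follow from the named method, compounded by a different interval without a reference value in section 9.1.

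This rests on a two-sided 95% interval, one day-1 result from each of 60 analysed patients, and the t-interval being applied to the success indicator. One-sided Wilson would remove the 55/60 conflict but not the one at 54/60, and would still need 70 patients. The study should correct this, but it does not invalidate the design.

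**What to change.** With N kept at 60:

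1. In section 9.1, replace the t-based interval for the success rate with the two-sided 95% Wilson interval for the day-1 success proportion.
2. In section 4.4, state that 54/60 gives a lower limit of about 80%, in place of the claim that it exceeds 82.5%.
3. Say before the data are seen which figure decides feasibility, in one of two ways:
   - At least 54 of 60 successes decides; the interval is descriptive and 82.5% is dropped as a criterion.
   - A two-sided Wilson lower limit above 82.5% decides (at least 56 of 60); 90% is kept as the planning assumption and the 27% chance of meeting the rule at a true 90% is stated.

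The second option sets a bar of 93.3% observed, above the 90% that section 4.4 calls adequate, so the sponsor should choose it only if excluding rates of 82.5% or lower is the aim. If the original precision is wanted instead, about 99 to 100 patients are needed.

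With N at 60 the change takes a few sentences and no further patients or data. The price is a less favourable stated precision, or a less favourable stated chance of a positive conclusion.

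### Section 4.4: with 60 participants and 90% success, the Wilson 95% lower limit is 79.9%, not above 82.5% as stated

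*Protocol*

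**What the plan says.** Section 4.4 treats 90% as the target performance: "A success rate of 90% is considered clinically sufficient based on previous studies (28-30) and HCPs' opinion". It then derives the sample size: "Calculated on 90% chance of success according Wilson standard error of proportions (CI95% > lower limit of 82.5%), 60 subjects are needed". The four elements are therefore an assumed success proportion of 90%, the Wilson method, a 95% confidence interval with a lower limit above 82.5%, and 60 participants. The section does not say whether the limit is one-sided or two-sided.

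The unit of analysis is one result per participant: "Only the first day of remote eCTG measurements will be used for determination of the feasibility", with one repeat on the same day allowed. Section 7.5 replaces patients who withdraw before the study interventions start, so 60 is the intended denominator.

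Section 9.1 reports the success rate as a number and percentage. For the confidence interval of the mean success rate it names a one-sample t-test, not Wilson.

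**The concern.** This sentence is the only quantitative justification of the sample size in the protocol, and it concerns the primary outcome. It tells the ethics committee and later readers that an observed 90% would exclude success rates of 82.5% and lower. If the named method gives a lower limit near 80%, then about one first-day failure in five remains compatible with a result exactly as planned, rather than about one in six (17.5%). A reader who repeats the calculation will not obtain 60 from the stated inputs.

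**Working it through.** **Inputs, all from section 4.4:** p = 0.90 (54/60), n = 60, 95% confidence, target lower limit 0.825. Because sidedness is not stated, both versions are shown: z = 1.960 (two-sided) and z = 1.645 (one-sided).

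**Attempt to reproduce the plan's figure with the named method.** The Wilson lower limit is

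[p + z²/2n − z·√(p(1−p)/n + z²/4n²)] / (1 + z²/n)

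- Two-sided: z² = 3.8415. Centre = (0.9 + 3.8415/120)/(1 + 3.8415/60) = 0.9320/1.0640 = 0.8759. Half-width = 0.0824/1.0640 = 0.0774. Interval 0.7985 to 0.9534, that is 79.9% to 95.3%.
- One-sided: z² = 2.7055. Lower limit = (0.9225 − 0.0676)/1.0451 = 0.8181, that is 81.8%.

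Neither exceeds 82.5%.

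**Sample size that the stated claim would need.** Setting the Wilson lower limit equal to 0.825 with an observed 0.90 gives n = z² × 0.825 × 0.175 / 0.075².

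- Two-sided: 98.6, so 99 (the limit is 82.47% at 98 and 82.52% at 99). A whole number of successes at exactly 90% makes it 100.
- One-sided: 69.4, so 70.

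**Other methods at 54/60, to see where 82.5% may come from:**

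| Method | Lower limit at n = 60 | n for 82.5% |
|---|---|---|
| Wilson, two-sided | 79.9% | 99 |
| Wilson, one-sided | 81.8% | 70 |
| Clopper-Pearson, two-sided | 79.5% | 103 |
| 90% minus the Wilson half-width | 82.3% | 64 |
| Wald, two-sided | 82.4% | 62 |
| Wald, one-sided | 83.6% | 44 |
| One-sample t interval (section 9.1) | 82.2% | not computed |

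Wald, two-sided: 0.90 − 1.96 × √(0.09/60) = 0.90 − 0.0759 = 0.8241, and n = 1.96² × 0.09/0.075² = 61.5, so 62. This lies close to both stated numbers and is their probable source.

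One-sided Wald does exceed 82.5% at 60, but it needs only 44 participants and so does not explain why 60 are needed.

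The t interval uses SE = √(0.09/59) = 0.0391 and t with 59 degrees of freedom = 2.001: 0.90 − 0.0782 = 0.822.

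**What 60 participants can show about 82.5%.** The two-sided Wilson lower limit is 81.9% at 55/60 and 84.1% at 56/60, so at least 56 successes (93.3%) are needed for it to exceed 82.5%. The binomial probability of 56 or more out of 60 is 27% at a true rate of 90%, 47% at 92% and 82% at 95%.

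**The case against.** The wording is "according Wilson standard error of proportions", which could be read more loosely than the Wilson score interval. If the author subtracted the Wilson half-width from 90%, or used Wald under the wrong name, the limit is 82.3% or 82.4%, and the gap shrinks to 0.1 to 0.2 points and two to four participants. On that view the fault is a wrong label plus rounding, and 60 is close to right for the calculation actually done. This stands as an explanation of how the number arose. It does not rescue the sentence: the score interval is the natural meaning of the name, and none of the two-sided versions checked exceeds 82.5% at 60.

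A second objection is that the study may never report a Wilson interval, since section 9.1 plans a t-based one. That is so, and at 54/60 its lower limit of 82.2% misses by only 0.3 points. It still misses, and the protocol then has two interval methods for one endpoint, which is a reason to align the two sections.

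A reader might go further and infer that a device performing as assumed would fail the study's feasibility criterion. The protocol does not support this. The figure of 82.5% appears only in the sample-size sentence, as a precision target. The one statement of adequacy is that 90% is clinically sufficient, and section 9.1 contains no test against 82.5% and no threshold on the interval. The 56/60 requirement and its probabilities therefore matter only if the sponsor intends 82.5% as a limit to be excluded.

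**Conclusion.** The precision stated in section 4.4 is wrong as written. With the named method, 60 participants and 90% observed success give a lower limit of 79.9% (two-sided) or 81.8% (one-sided), against a stated limit above 82.5%: a shortfall of 2.6 or 0.7 percentage points. Meeting the statement would need about 99 or 70 participants.

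This rests on reading the named method as the Wilson score interval and on 60 independent first-day outcomes, one per participant. That the Wald formula is the source is an inference from how closely its figures match. The finding does not show that 60 is too few for a feasibility cohort, nor that any criterion would be failed. It shows that the published justification does not follow from its own inputs.

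**What to change.** Keep 60 participants. Replace the sample-size sentence in section 4.4 with: *With 60 participants and 54 successes (90%), the two-sided 95% Wilson interval is 79.9% to 95.3%.* Delete the claim that the lower limit exceeds 82.5%. Putting 79.9% into the existing sentence would not be enough: the limit is 79.85%, so it does not strictly exceed 79.9%, and the wording would still present 60 as derived from a target.

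In section 9.1, name the same two-sided 95% Wilson interval for the success proportion in place of the one-sample t-test interval.

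Only if the sponsor does mean 82.5% as a limit to exclude, say so, and state that this needs at least 56 of 60 successes, with a probability of 27%, 47% or 82% at a true rate of 90%, 92% or 95%.

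The cost is one sentence in each of two sections and a less favourable stated figure. No patients are added and no procedure changes.
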